### Longitudinal modulation of the peripheral immune status

3.2

The interims analysis reveals that the tumor surgery and the subsequent RCT lead to systemic immune modulations in absolute cell counts of different cell types of the innate and adaptive immune system. Additionally, significant changes in the expression of activation markers on these immune cell types can be detected (see **Figures 2**, **3**). The immunological data presented here is not covering the follow-up data of all patients, as not all patients have completed the follow-up at the time of evaluation and some patients decided to undergo RCT at another clinic and were thus not available for the follow-up time points.

**Figure 2 f2:**
[figure not shown]
Longitudinal determination of immune cell counts within the ImmunBio-KHT trial: The patients’ systemic immune status was determined from peripheral blood via flow cytometry-based immunophenotyping. Absolute immune cell counts were calculated for all cell types analyzed longitudinally. In **(A)** the counts of DCs over all three time points are depicted. In **(B, C)** the counts of the eosinophilic and neutrophilic granulocytes are depicted, respectively, whereas in **(D)** the counts of mMDSCs and in **(E)** the B cell counts are shown. In **(F)** the T cell counts are depicted and in **(G)** the monocyte and in **(H)** the gMDSC cell counts are shown. The line in each graph shows the median cell count. The Kruskal-Wallis test was applied on all data sets and the significance levels were calculated based on the change from the initial time point (01). (01: n=136, 02: n=56, 03: n=46, *p value ≤ 0.5, ***p value ≤ 0.001, **p<0.01, ****p<0.0001).

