### Study design and registration

2.1

This prospective, observatory, multicenter trial monitors the local and peripheral immune status and the microbiome of newly diagnosed HNSCC patients (intervention cohort) throughout their treatment. In addition, the equivalent data set of a control cohort will be collected from cancer-free patients that undergo non-cancer surgery of the head-and-neck region. The patients of the intervention cohort undergo ablative surgery and adjuvant RCT or definitive RCT. For the determination of the peripheral immune status, whole blood is taken before surgery, on day seven post-surgery and at the end of RCT. In addition, the oral, tumor and the bowel microbiome is sampled before (stool and saliva samples) and during the surgery (tumor microbiome sample). Also, the local immune status from the tumor tissue is determined after tumor excision by pathological assessment (see **Figure 1**). Oncological data of the patients is followed-up according to the clinical routine or until the death of the patient. In the control cohort, the peripheral immune status is also determined from whole blood before and seven days after surgery. The microbiome is sampled as well (see **Figure 1**).

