### Clinical characteristics

3.1

After the recruitment of 150 patients in the study cohort and the first five patients in the control cohort in November 2023 at the University of Erlangen only, a first analysis of the clinical characteristics and the immune status of the patients was performed. The clinical characteristics of the patients have been summarized in **Table 2**.

**Table 2 T2:** Clinical characteristics.

Patient characteristics of the first 150 patients of the ImmunBioKHT trial		
Intervention cohort		
Factor	Category	N
Total number		150
Age (years)	Mean Range	66
		31 - 92
Gender	Male	102
	Female	48
Cancer location	Larynx	27
	Hypopharynx	11
	Oropharynx	44
	Nasopharynx	2
	Oral cavity	64
	Other	2
P16 status	Positive	17
	Negative	27
	No oropharyngeal cancer	106
cT classification	T0	4
	T1	23
	T2	39
	T3	22
	T4	5
	T4a	29
	T4b	3
	N/A	25
cN classification	N0	55
	N1	17
	N2	2
	N2a	5
	N2b	24
	N2c	10
	N3	0
	N3a	0
	N3b	11
	N/A	26
cM classification	M0	96
	M1	11
	Distant metastases expected, cannot be assessed	15
	N/A	28
Smoker’s history	Current smoking	62
	Quit smoking	12
	Never	9
	N/A	67
Alcohol consumption	Yes	32
	No	17
	N/A	101
	Definitive RCT	20
Radio-Chemotherapy	Adjuvant RCT	25
	No RT	57
	N/A	48
Control cohort		
Factor	Category	N
Total number		5
Age	Mean	29
	Range	23 - 35
Gender	Male	2
	Female	3
Performed surgery	Bignathe corrective osteotomy	5
Smoker’s history	Still smoking	0
	Quit smoking	1
	Never	4
	N/A	0
Alcohol consumption	Yes	2
	No	3
	N/A	0

In the intervention cohort, the mean age of the patients was 66 years at study entry, whereas the mean age in the control cohort was 29 years. Thus, at this point, the control cohort is not yet comparable to the intervention cohort in terms of the age. Nonetheless, by further recruitment of patients in the control cohort, this difference will be minimized in the future. In the control cohort, all five patients that have been recruited so far did receive a bignathe corrective osteotomy, as this surgery induces a comparable trauma as the tumor surgery of the HNSCC patients in the intervention cohort (see **Table 2**).

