Regarding the intervention cohort, the distribution of the gender of the patients, reflects the normal clinical situation, as around twice as much male patients than female patients have been recruited. In the intervention cohort, the cancer entities of two patients have been summarized as “other” in **Table 2**. One of these patients was diagnosed with thyroid cancer and one patient suffered from a cervical CUP syndrome. The therapy that was applied after the tumor surgery has been assessed as well. For 48 patients however, the therapy has not yet been finished and is thus not yet documented in the affiliated trial data base. Moreover, the TNM classification for the patients of the intervention cohort has been performed. For 25 patients however, the data is not available yet at this time. The HPV testing (p16 status) has only been performed for patients that have been diagnosed with oropharyngeal cancer, as there is no known predictive value of the HPV testing in other HNSCC locations. Finally, as HPV infections are not the only risk factor for HNSCC, but also alcohol and tobacco consumption, the smoker’s history and the consumption of alcohol have been queried in both patient cohorts. However, many patients in the intervention cohort refused to provide information on their nicotine and alcohol consumption. In the control cohort on the other hand, the patient number at this time is too low to compare the noxious behavior to the intervention cohort (see **Table 2**).

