Postoperatively, a significant increase of eosinophilic and neutrophilic granulocytes (**Figures 2B, C**) and of monocytes (**Figure 2G**) has been detected in the peripheral blood. In addition, a significant increase in the percentage of monocytic myeloid-derived suppressor cells (MDSCs) and granulocytic MDSCs has been found (**Figures 2D, H**). The cells of the adaptive immune system, namely the B cells and T cells decreased in the periphery postoperatively (**Figures 2E, F**). A significant decrease in absolute cell counts has also been noticed for the dendritic cells (DCs) on day 7 after surgery (**Figure 2A**). The RCT however, caused a general decline of the immune cell counts in the periphery for all presented immune cell populations. A significant decline has been detected for the DCs (**Figure 2A**), the B cells (**Figure 2E**) and the T cells (**Figure 2F**). For the eosinophils (**Figure 2B**) and the neutrophils (**Figure 2C**), the cell counts generally decreased to the initial level that has been determined before therapy. Even though the cell counts of the monocytic MDSCs (**Figure 2D**) declined after RCT, they were still significantly higher than before surgery. For the granulocytic MDSCs on the other hand, the cell counts declined below the initial median cell count, even though this change was not statistically significant. In sum, a dynamic modulation of the different immune cell subsets has been detected during this therapeutic setting.

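### Figures 2 and 3 test change over time with Kruskal-Wallis on 136, 56 and 46 samples from one cohort, so treatment change cannot be separated from a change in patient mix.

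*Protocol article*

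**What the plan says.** Section 2.1 (Study design and registration) describes repeated sampling of the same patients: "whole blood is taken before surgery, on day seven post-surgery and at the end of RCT". It gives two treatment paths, surgery with adjuvant RCT or definitive RCT.

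The legends of Figures 2 and 3 name the same test for cell counts and activation markers: "The Kruskal-Wallis test was applied on all data sets and the significance levels were calculated based on the change from the initial time point". Both give the same numbers: "01: n=136, 02: n=56, 03: n=46".

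Section 3.2 explains that follow-up was incomplete at the time of evaluation and that "some patients decided to undergo RCT at another clinic and were thus not available for the follow-up time points". It then concludes: "The RCT however, caused a general decline of the immune cell counts in the periphery for all presented immune cell populations". The Discussion goes further and treats immune modulation by surgery and RCT as already proven.

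Table 2 (section 3.1) gives therapy for the 150 patients: "Definitive RCT 20", "Adjuvant RCT 25", 57 with no radiotherapy and 48 not available. Of the last group the text says: "For 48 patients however, the therapy has not yet been finished".

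**The concern.** There are two separate problems.

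- **Pairing is ignored.** Kruskal-Wallis treats the three sets of values as independent groups. Samples from one patient are correlated, and within-patient change is not what the test assesses. The legend speaks of change from the first time point, but 136 values at 01 against 56 and 46 do not fit a paired analysis.
- **The patients differ between time points.** Time point 01 includes patients who never receive radiotherapy, and time point 03 cannot. Whether a patient receives RCT is a clinical choice, so equal baseline immune status cannot be assumed, and no baseline comparison is reported. A difference between 03 and 01 can then reflect treatment, a different set of patients, or both.

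What is at stake is the reading of the first interim results. Section 2.7 gives this analysis the aim of depicting longitudinal change, and section 3.2 and the Discussion read the differences causally.

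**Working it through.** **Step 1: counting.** The inputs are Table 2 and the figure legends.

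- Most pairs possible: 56/136 = 41% of baseline patients for 01-02, and 46/136 = 34% for 01-03.
- Patients not recorded as having no radiotherapy: 150 − 57 = 93. At least 136 − 93 = 43 of the 136 baseline patients (43/136 = 32%) therefore had none. They count at 01 and cannot count at 03.
- Definitive-RCT patients follow the path without surgery, so by design they have no post-surgery sample, yet they may count at 03. The sets at 02 and 03 may overlap only in part.
- Documented RCT: 20 + 25 = 45 patients, against 46 samples at 03. At least one of these samples comes from a patient whose therapy is undocumented, and the split of the 46 by treatment path is not given.

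**Step 2: which contrasts were tested.** Significance is given only against 01. Section 3.2 says that after RCT eosinophils and neutrophils returned to about the initial level, and that monocytic MDSCs stayed above it. For these cells the decline attributed to RCT is a 02-to-03 difference. No test is reported for it, the patient sets need not match, and it cannot be told apart from recovery after the day-7 surgical rise.

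**Step 3: possible size.** The article states no figure to reproduce, so this is a simulation on assumptions. Value at 01 = patient level + error; value at 03 = the same patient level + new error + true change. Total SD is 1 and the within-patient correlation is 0.3, 0.5 or 0.7. There are 136 patients at 01, 46 of them at 03, and 56 drawn at random at 02. In some settings the 46 have a patient level lower by *d* = 0.3 or 0.5 SD. The test level is two-sided 0.05 (the legends print 0.5 as the lowest level, which I take to mean 0.05). Correlation, *d* and true change are not in the document.

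If nothing changes within patients, the expected spurious difference between 03 and 01 is *d* × (1 − 46/136) = 0.66*d*, that is 0.20 SD for *d* = 0.3 and 0.33 SD for *d* = 0.5.

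Rejection rates with no true change, over the three correlations:

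| Baseline difference *d* | Three-group Kruskal-Wallis | Unpaired 01 v 03 (Mann-Whitney) | Paired 01-03 (signed-rank) |
|---|---|---|---|
| 0 | about 1-3% | about 1.6-3.2% | about 5% |
| 0.3 SD | about 10-13% | about 16-18% | about 5% |
| 0.5 SD | about 33-37% | about 44-47% | about 5% |

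Power for a true 0.3 SD change with no baseline difference:

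| Correlation | Unpaired 01 v 03 | Paired |
|---|---|---|
| 0.3 | about 40% | about 38% |
| 0.5-0.7 | about 38% | about 50-71% |

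A mix effect can also hide a real change. With a true 0.4 SD change and a 0.5 SD baseline difference in the opposite direction, Kruskal-Wallis rejected in only 1.5-4.5% of runs.

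**The case against.** The case on the other side has real content.

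- **No bias is demonstrated.** Different mix produces bias only if RCT and non-RCT patients differ at baseline in the marker concerned, and the document gives no such figure. Without a difference the unpaired test is conservative, so reported significance was harder to reach. This stands.
- **Strong results may survive.** The legends use levels down to p<0.0001. An assumed shift of 0.3 SD alone reached that level in about 0.1% of simulated cases, and 0.5 SD in about 0.4-1.0%. The figures are not available here, so it is not known which markers reached which level. This also stands.
- **Pairing does not always gain power.** At correlation 0.3 the paired test has no advantage, because it drops 136 − 46 = 90 baseline values. This stands, but it concerns power only; the paired test is still the one protected against a change in mix.
- **The incomplete follow-up is disclosed and the interim is exploratory.** True, but disclosure does not support the causal wording.

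A reader might infer three stronger conclusions that the documents do not support. First, that the reported changes are false: only inseparability is shown. Second, that the same test will be used at 500 and 800 patients and will select wrong markers. Section 2.7 fixes no test for those interims and leaves modelling to separate data-mining approaches, and section 2.4 plans cluster analysis for the primary endpoint. Third, that the set at 03 consists of 20 definitive and 25 adjuvant patients: those are whole-cohort counts, they sum to 45 rather than 46, and some patients had RCT elsewhere.

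**Conclusion.** The concern holds in limited form. The test does not fit repeated samples of one cohort, and the mix at 01 must differ from that at 03, since at least 43 of 136 baseline patients cannot contribute to 03. Treatment change and patient mix therefore cannot be separated in Figures 2 and 3, and the statement that RCT caused a decline goes beyond this analysis.

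The counting rests on the document alone. The error rates depend on the assumed correlation and baseline difference: anywhere from conservative when there is no difference to several times the nominal 5% at 0.3-0.5 SD. The defect lies in the reported interim analysis and its interpretation. It does not reach the signature-building plan, for which no such test is specified.

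**What to change.** 1. Reanalyse Figures 2 and 3 with Wilcoxon signed-rank in patients who have both samples: 01-02, 01-03, and 02-03 in adjuvant-RCT patients. A mixed model with a patient random effect is an alternative.
2. Report the number of pairs for each contrast.
3. Compare baseline values of patients with and without each follow-up sample.
4. Show adjuvant and definitive RCT separately where therapy is documented. A model of time by treatment path cannot yet cover everyone, because therapy is missing for 48 of 150.
5. In section 3.2 and the Discussion, replace causal wording with a description of observed within-patient change.
6. Use the same paired approach for any longitudinal comparison at the 500 and 800 interims, where the test is still open.

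The cost is a reanalysis of existing data and a few sentences of text. Each contrast rests on fewer patients (at most 56 pairs for 01-02 and 46 for 01-03), and the path-specific estimates will be less precise, with only 20 definitive and 25 adjuvant RCT patients documented so far.

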**Figure 3 f3:**
[figure not shown]
Longitudinal determination of the activation status of immune cells within the ImmunBio-KHT trial: The patients’ immune status was determined from peripheral blood via flow cytometry-based immunophenotyping. The expression of several activation markers was determined and the percentage of positive cells were calculated. Graph **(A)** shows the percentage of CD69 positive T Helper cells and **(B)** of T Killer cells, respectively. The expression of CD25 on basophils is depicted in **(C)**, the expression of HLA-DR on monocytes is shown in **(D)** and the percentage of HLA-DR positive T cells in shown in **(E)**. In **(F)** the HLA-DR expression on NK cells is depicted, while **(G, H)** show the percentage of PD1 positive T Killer and T Helper cells. The line in each graph shows the median percentage of positive cells. The Kruskal-Wallis test was applied on all data sets and the significance levels were calculated based on the change from the initial time point (01). (01: n=136, 02: n=56, 03: n=46, *p value of ≤0.5, **p<0.01, ***p<0.001,****p<0.0001).

Postoperatively, a significant increase of eosinophilic and neutrophilic granulocytes (**Figures 2B, C**) and of monocytes (**Figure 2G**) has been detected in the peripheral blood. In addition, a significant increase in the percentage of monocytic myeloid-derived suppressor cells (MDSCs) and granulocytic MDSCs has been found (**Figures 2D, H**). The cells of the adaptive immune system, namely the B cells and T cells decreased in the periphery postoperatively (**Figures 2E, F**). A significant decrease in absolute cell counts has also been noticed for the dendritic cells (DCs) on day 7 after surgery (**Figure 2A**). The RCT however, caused a general decline of the immune cell counts in the periphery for all presented immune cell populations. A significant decline has been detected for the DCs (**Figure 2A**), the B cells (**Figure 2E**) and the T cells (**Figure 2F**). For the eosinophils (**Figure 2B**) and the neutrophils (**Figure 2C**), the cell counts generally decreased to the initial level that has been determined before therapy. Even though the cell counts of the monocytic MDSCs (**Figure 2D**) declined after RCT, they were still significantly higher than before surgery. For the granulocytic MDSCs on the other hand, the cell counts declined below the initial median cell count, even though this change was not statistically significant. In sum, a dynamic modulation of the different immune cell subsets has been detected during this therapeutic setting.

The applied therapy had a significant effect not only on the cell counts, but also on the activation status of different immune cell populations (**Figure 3**). A significant upregulation of activation markers has mostly, but not exclusively been detected after RCT on several immune cell populations. On T Helper cells for instance, a significant increase in CD69 expression (**Figure 3A**), but also in PD1 (**Figure 3H**) expression has been detected. For the cytotoxic T cells, the same modulations in the activation state have been detected (**Figures 3B, G**). Furthermore, an increased CD25 expression has been found for the basophilic granulocytes (**Figure 3C**). Even though HLA-DR cannot be considered as a classical activation marker, it is included in our assay since a modulation of the expression of HLA-DR is commonly detected on immune cells. Since HLA-DR is a key molecule in antigen presentation, its differential expression might be relevant in tumor immunology. For T cells and NK cells, an increase in HLA-DR positive cells has been found after RCT (**Figures 3E, F**). On the other hand, HLA-DR positive monocytes were significantly reduced postoperatively but remained unchanged until after the RCT (**Figure 3D**).

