Nowadays, it is evident that singular immunological biomarkers are most likely not sufficient to predict outcome. As the tumor immune response is complex and involves numerous cell types and structures throughout the whole organism, combined immunological scores that involve local immune markers from the tumor tissue and peripheral immune parameters from whole blood (or even including the microbiome composition) should be more promising (5, 17, 21). Such immunological scores are already successfully applied for the classification of colon cancer (22) and could potentially improve the grading and treatment of HNSCC as well and might also predict therapy failure patterns of radiotherapy (RT) in HNSCC (23).

In order to define prognostic immune signatures for HNSCC, the ImmunBio-KHT trial was initiated as interdisciplinary study between ENT-surgery, maxillofacial-surgery and radiation oncology in 2022. This trial aims to set up a heterogeneous, real-world cohort of HNSCC patients undergoing tumor surgery and/or radio-chemotherapy to define prognostic immune matrices. These immune signatures are built from immune markers from the tumor tissue, the peripheral blood, as well as from the microbiome with the objective to create a basis for personalized treatment of HNSCC in the future.

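### Section 3.2 says RCT caused the fall in cell counts, but the pooled, unpaired analysis cannot separate RCT from surgery and surgical recovery in adjuvant patients

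*Protocol article*

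**What the plan says.** Section 2.1 of the protocol article fixes three blood samples in the tumor cohort: "whole blood is taken before surgery, on day seven post-surgery and at the end of RCT". Controls have two: "In the control cohort, the peripheral immune status is also determined from whole blood before and seven days after surgery". On treatment, the same section says "The patients of the intervention cohort undergo ablative surgery and adjuvant RCT or definitive RCT", and the Introduction describes the cohort as "HNSCC patients undergoing tumor surgery and/or radio-chemotherapy".

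The Figure 2 and Figure 3 legends report a Kruskal-Wallis test on 136, 56 and 46 samples at time points 01, 02 and 03, and say that "the significance levels were calculated based on the change from the initial time point (01". Neither legend mentions a split by treatment path.

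Section 3.2 then states: "The RCT however, caused a general decline of the immune cell counts in the periphery for all presented immune cell populations". For eosinophils and neutrophils, the same paragraph adds that "the cell counts generally decreased to the initial level that has been determined before therapy".

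**The concern.** The sentence is causal and covers every population shown. A decline can be credited to RCT only if the comparison isolates RCT. In adjuvant patients, 01 to 03 spans surgery, recovery and RCT, and 02 to 03 spans recovery and RCT. Nothing in the sampling scheme separates the parts: there is no sample after recovery and just before RCT, and no late control sample to show the course after surgery alone. More recruitment under the same schedule will not change this.

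Pooling adds a second problem. A patient treated by definitive RCT without surgery has no post-surgery sample and cannot contribute to a fall from day 7, yet may be counted at time point 03. Patients without radiotherapy can contribute to 01 and 02 but not to a post-RCT sample. An unpaired comparison can show such shifts in patient mix as treatment effects.

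At stake is how the longitudinal data are read. The primary endpoint (section 2.4) is change in immune matrices over these time points, and further interim analyses are planned at 500 and 800 patients (section 2.7).

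**Working it through.** **1. Table 2, radio-chemotherapy rows.** Definitive 20, adjuvant 25, no RT 57, not available 48. Sum: 20 + 25 + 57 + 48 = 150, which reproduces the stated cohort total.

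**2. Treatment paths among documented RCT patients.** 20 + 25 = 45. Definitive share: 20/45 = 44.4% (Wilson 95% interval 30.9% to 58.8%). This describes Table 2, not the 46 samples at time point 03.

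**3. What the sample counts imply** (one sample per patient and time point).
- Time point 01: 136 − 45 = 91, so at least 91 samples come from patients with no documented RCT.
- Time point 02: 56 − 25 = 31, so at least 31 samples come from patients not documented as adjuvant RCT.
- Time point 03: 46 − 25 = 21, so at least 21 samples come from patients not documented as adjuvant RCT.
- Time point 03 against all documented RCT: 46 − 45 = 1 sample more than documented patients.

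Some of these patients may prove to be adjuvant cases once the 48 open records are completed. As documented, the three groups are not one set of patients followed through time.

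**4. Reported pattern by population (section 3.2, Figure 2).**

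| Population | Day 7 | After RCT, against time point 01 |
|---|---|---|
| Eosinophils | significant rise | back to the pre-therapy level |
| Neutrophils | significant rise | back to the pre-therapy level |
| Monocytic MDSCs | significant rise | still significantly higher |
| Granulocytic MDSCs | significant rise | below the initial median, not significant |
| Monocytes | significant rise | no separate result given |
| Dendritic cells | significant decrease | significant decline |
| B cells | decrease | significant decline |
| T cells | decrease | significant decline |

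Three of eight populations have a reported significant decline from baseline, and all three were already lower on day 7. For eosinophils and neutrophils, a rise followed by a return to baseline is compatible with recovery from surgery alone, with an RCT effect, or with both. A fall from day 7 would be judged by comparing 02 with 03, but significance is given only against 01.

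**5. Precision if split by path.** Assume complete pairs, two-sided alpha 0.05, 80% power and a normal approximation. The smallest detectable paired standardized change is (1.960 + 0.842)/√n:
- n = 20 (definitive): 0.63
- n = 25 (adjuvant): 0.56
- n = 45 (pooled): 0.42

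**The case against.** The strongest reply is that this is descriptive interim reporting. Section 2.7 says the first analysis is meant to depict longitudinal changes and show feasibility, and section 4 leaves the link to clinical data for later. No RCT effect is defined as an estimand, and stratification may be set out in an analysis plan that is not shown. The paragraph also openly reports the returns to baseline and the non-significant result, and a return from a raised day-7 level is literally a decline. All of this stands and limits the weight of the point. It does not rescue the causal verb or its extension to every population.

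The reply also rightly blocks several stronger readings that a reader might infer:

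- *That no sample can isolate RCT in anyone.* In definitive-RCT patients without surgery, 01 to 03 contains no operation. The limit applies to adjuvant patients.
- *That 44% of the time point 03 samples come from patients without surgery.* The mix of the 46 is not given. The absence of surgery is inferred from the term definitive RCT, the Introduction and section 2.1. The Figure 1 legend and section 3.1 read as if all patients had surgery. If they did, the confounding covers everyone.
- *That 46 against 45 is an error.* Section 3.1 says "For 48 patients however, the therapy has not yet been finished" and is not yet in the database. One pending record would explain it.
- *That a core aim of the trial is damaged.* The separation sought in section 4 is surgical trauma from tumor removal, and a prognostic signature can use a post-treatment value whichever treatment produced it.
- *That day 7 is the peak of surgical trauma.* The article gives no time course.

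**Conclusion.** The point holds in a limited form: the attribution to RCT in section 3.2 is not supported by the analysis as reported. In adjuvant patients the RCT effect is mixed with surgery or recovery, treatment paths are pooled at time point 03, and the test ignores within-patient pairing. The reported results support a significant decline from baseline after treatment in three of eight populations, without assigning it to RCT.

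A reader might go further and conclude that RCT has no effect on these counts. The documents do not show that. They show only that this comparison cannot tell.

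The conclusion rests on the sampling times in section 2.1 and on the legends describing the whole comparison. It does not depend on the 44% share or on the one-sample surplus. How far pooling alters the result cannot be computed, because the treatment path of the 46 samples is not reported.

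**What to change.** 1. In section 3.2, replace *caused* with *after RCT*, and limit the statement to populations with a reported significant change from baseline, giving the direction of each.
2. In this and later interim analyses, use within-patient comparisons stratified by treatment path. For definitive-RCT patients, report 01 to 03 as the change over RCT without surgery, noting that there is still no comparator without RCT. For adjuvant patients, report 01, 02 and 03 as the combined course of surgery plus RCT, and do not read 02 to 03 as a pure RCT effect.
3. Confirm from treatment records which definitive-RCT patients had surgery, and reconcile the Introduction and section 2.1 with the Figure 1 legend and section 3.1.
4. Report the treatment path of each of the 46 samples at time point 03.

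This uses existing samples and needs a record check and a re-analysis. The cost is precision: with the currently documented 20 and 25 patients, the detectable paired change is about 0.63 and 0.56 standard deviations, against 0.42 pooled. The loss should shrink as recruitment continues.
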